## Randomisation

Following confirmation of informed consent, eligibility and completion of baseline assessments, patients will be randomised by an authorised member of the research team at the site. Patients will be randomised in a 1:1 allocation ratio, to receive either HSF or APM. Randomisation will be performed using minimisation, incorporating a random element, via a central 24-hour automated telephone randomisation system based at the Leeds Institute of Clinical Trials Research (LICTR). The dynamic allocation method should ensure intervention groups are well balanced for the following minimisation/stratification factors:CentrePU status (no pressure ulcer, Category 1, Category 2)Secondary care hospital, community hospital, intermediate care or rehabilitation facilityMethod of consent (written OR witnessed verbal OR consultee or nearest relative/guardian/welfare attorney (Scotland) agreement)

The randomisation system will include an automated internal check using NHS numbers to confirm that the patient has not been recruited to the trial previously.

In addition, at the time of randomisation, 10% of patients will be randomly selected for expert clinical assessment and photography.

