### Primary endpoint analysis

#### Primary analysis

A Cox proportional hazards model (after confirming the proportional hazards assumption is valid) will be fitted to the primary endpoint, with adjustment for the minimisation factors: healthcare setting, PU status and consent, and the following covariates: presence of pain on a healthy, altered or Category 1 PU skin site, conditions affecting peripheral circulation and treatment group. Centre will be assessed for inclusion as a random effect. The hazard ratio for the estimate of the treatment effect and adjusted confidence interval corresponding to the nominal *p* value will be presented. Patients who do not develop a Category 2 or above PU during the treatment phase or by 30 days post treatment follow-up will be censored at the date of their last evaluable skin assessment.

Kaplan-Meier estimates of the probability of patients developing a Category 2 or above PU over 90 days in each group and adjusted confidence intervals corresponding to the nominal *p* value will be presented.

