#### Secondary endpoint analysis

The secondary endpoints, time to developing a PU of at least Category 1, and time to developing a PU of at least Category 3, will be analysed using Cox proportional hazards modelling (after confirming the proportional hazards assumption is valid) adjusting for the minimisation factors and same covariates as for the primary endpoint analysis and treatment group.

A Cox proportional hazards model (after confirming the proportional hazards assumption is valid) will be fitted to the outcome time to healing of pre-existing Category 2 PUs; covariates fitted in the primary endpoint model will be assessed for inclusion and treatment group.

A substudy analysis will be performed to examine the PU-QoL-P instrument responsiveness; effect sizes [29] and standardised response means (SRM) [30] before and after mattress allocation will be estimated. Independent *t* tests will be conducted to assess the ability of the PU-QoL-P instrument to distinguish between patients whose PUs deteriorate or heal. Subject to the results of the instrument responsiveness analysis, QoL domains and subscales for the SF-12 and PU-QoL-P will be compared between treatment groups using multilevel repeated measures modeling allowing for time, mattress type, mattress type by time interaction, adjusting for baseline QoL, patient and patient by time interaction as random effects.

Adverse events and serious adverse events classified as related to the mattress, resulting from administration of any research procedures, and falls and device-related events during the treatment phase and follow-up will be listed and summarised by treatment group.

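### The SF-12 and PU-QoL-P model leaves out the minimisation factors that the primary and Category 1 and 3 models adjust for: a minor point with an almost free fix

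*Protocol article*

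**What the plan says.** All references are to the Protocol article.

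- **Randomisation:** "Randomisation will be performed using minimisation, incorporating a random element", in a 1:1 ratio. On its purpose: "The dynamic allocation method should ensure intervention groups are well balanced for the following minimisation/stratification factors". The factors are centre, PU status (three levels), type of facility, and route of consent (three levels).
- **Primary analysis:** a Cox model "with adjustment for the minimisation factors: healthcare setting, PU status and consent", with centre considered as a random effect.
- **Secondary endpoint analysis, Category 1 and Category 3 ulcers:** Cox models "adjusting for the minimisation factors and same covariates as for the primary endpoint analysis and treatment group". The healing model considers the primary model's covariates for inclusion.
- **Secondary endpoint analysis, quality of life:** subject to the responsiveness results, SF-12 and PU-QoL-P are compared by "multilevel repeated measures modeling allowing for time, mattress type, mattress type by time interaction, adjusting for baseline QoL, patient and patient by time interaction as" the random terms. No allocation factor appears, centre is not mentioned, and no reason is given.
- **Missing data:** missingness will be examined over time and by arm. Multiple imputation is a possibility under missing at random, and pattern mixture models under missing not at random. The imputation variables are not named.

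**The concern.** Minimisation makes the arms alike on the factors that it uses. If those factors also predict the outcome, a model without them leaves their variation in the residual. The model-based standard error then ignores the balance that the design achieved. It is too large, the test runs below its nominal level, and some power is lost.

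Baseline quality of life takes up part of this variation but need not take up all of it. PU status at entry could well predict later scores on a pressure-ulcer instrument, even at a given baseline score.

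Health-related quality of life is a listed secondary objective. Its model is the only treatment-comparison model in the two analysis sections that neither includes nor considers the allocation factors.

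There is a second, weaker strand. A repeated-measures model relies on data being missing at random given what is in the model. The quality-of-life forms at weeks 1 and 3 are listed among the treatment-phase assessments. That phase can end once a patient is no longer at high risk, which requires among other things that no ulcer of Category 1 or above is present. Completion may therefore depend on PU status.

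**Working it through.** **Plan's own figure.** The article gives no standard deviation, effect size or power for the quality-of-life comparison, so there is nothing to reproduce on this point. The residual R² below is an assumption.

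**Inputs**
- Two-sided 5% level (Sample size); 1:1 allocation and the minimisation factors (Randomisation).
- About 500 patients for PU-QoL-P (Sample size).
- R²: the share of outcome variance left after baseline quality of life that the omitted factors explain. Not in the article; assumed 0 to 10%.

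**Step 1: precision.** With balanced factors, the unadjusted standard error exceeds the adjusted one by k = 1/√(1 − R²).
- Actual type I error = 2 × [1 − Φ(1.96k)].
- Actual coverage = 2Φ(1.96k) − 1.
- Power where the adjusted analysis has 80% = Φ(2.80 − 1.96k).

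| Assumed R² | k | Interval wider by | Coverage | Type I error | Power (80% if adjusted) |
|---|---|---|---|---|---|
| 0 | 1.000 | 0% | 95.0% | 5.0% | 80% |
| 1% | 1.005 | 0.5% | 95.1% | 4.9% | – |
| 2% | 1.010 | 1.0% | 95.2% | 4.8% | – |
| 5% | 1.026 | 2.6% | 95.6% | 4.4% | 79% |
| 10% | 1.054 | 5.4% | 96.1% | 3.9% | 77% |

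For example, at R² = 10%, k = 1/√0.90 = 1.054, 1.96 × 1.054 = 2.066, and 2 × [1 − Φ(2.066)] = 0.039.

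**Step 2: simulation of minimisation.** The set-up was 500 patients, minimisation on four factors with an assumed allocation probability of 0.8, 20 assumed centres, one post-baseline outcome and 2,500 runs. At R² = 5% and 10% the unadjusted type I error was 4.7% and 3.5%, the adjusted one 5.2% and 4.9%, and the standard-error ratio 1.026 and 1.054. The Monte Carlo error is √(0.05 × 0.95/2500) = 0.44 percentage points. The 5% case therefore cannot be told apart from nominal; the 10% case can.

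**Step 3: dropout.** A single-follow-up analysis of covariance with no true effect, with allocation balanced within three PU-status levels, gave:
- Dropout depends on PU status equally in both arms: bias about 0, with or without the factor in the model.
- Dropout depends on PU status differently by arm (assumed 10%, 30% and 50% by status in one arm, a flat 25% in the other): unadjusted bias about 0.03, 0.04 and 0.06 SD at R² = 2%, 5% and 10%; adjusted bias about 0.

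**The case against.** **The article is a condensation.** It says that analysis plans will be finalised before any analysis, and a full covariate list for a secondary model is often left to them. This would answer a complaint that the model is incompletely described. It does not fully answer this one. The sentence names an adjustment set, baseline quality of life, in the same section that adjusts two other models for the minimisation factors. That is a stated model which differs from its neighbours. A later plan may still add the factors.

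**The loss is unproven and may be nil.** This stands. Baseline quality of life is recorded at the same assessment as PU status and carries part of its effect. A reader might infer that the intervals are definitely too wide, or take R² = 20% (k = 1.118, type I error 2.8%, power 73%) as the size. Nothing in the article supports a value that high once baseline is in the model.

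**Missing data.** A reader might also infer that the omission biases the mattress comparison through dropout. The article does not show this: bias needs an omitted factor to act on dropout differently by arm, and the pattern in step 3 is a strong one. An arm difference is conceivable, since the trial is open and the Background reports that some patients dislike alternating-pressure mattresses, but it is not established. The Missing data section leaves room for imputation using these factors, though it does not promise it.

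**Consent method adds little for SF-12.** This also stands. Proxy completion is described for PUQoL-UI and EQ-5D-5L only, so patients entered through a consultee will largely lack SF-12 data.

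**The simulations are simplified.** They use one follow-up rather than the repeated-measures model. They support the direction and rough size, no more.

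**Conclusion.** The point holds as a minor inconsistency worth correcting. The quality-of-life model omits the factors on which patients were allocated, while the primary and the Category 1 and 3 models adjust for them.

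The consequence is conservative: intervals 0 to 5.4% wider and a type I error between 5.0% and about 3.9%, for an assumed residual R² of 0 to 10%. Both ends rest on that assumption. The type I figures also assume that the balance carries over to the patients with quality-of-life data. In the PU-QoL-P subset it may be looser, which would bring the error nearer to 5%.

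The omission does not itself bias the treatment comparison and does not raise the false-positive rate when data are complete or dropout acts alike in both arms. The primary analysis is untouched.

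**What to change.** In Secondary endpoint analysis, specify the SF-12 and PU-QoL-P model as follows:

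- Fixed effects: time, mattress, mattress by time, baseline quality of life, PU status and healthcare setting. Add method of consent where the instrument has data at more than one of its levels.
- Random effects: patient and patient by time as now, with centre assessed for inclusion as in the primary analysis.
- In Missing data, state that any imputation model will include the same factors.

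The cost is a line or two of wording. The factors are needed to randomise, so they should be on record for every patient. With three levels each, the fixed effects use 2 + 2 + 2 = 6 degrees of freedom (one more if intermediate care and rehabilitation are separate levels). That is negligible against about 500 patients or more.

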#### Assessment of the feasibility of the blinded outcome assessment

To assess the feasibility of the blinded outcome assessment using photography and blinded endpoint review, a sensitivity analysis of the primary endpoint analysis will be conducted to assess the risk of over-reporting of category 2 or above PUs, replacing the primary endpoint for those patients with a Category 2 or above PU with the assessment made in the blinded central endpoint review. To assess under-reporting of the development of Category 2 or above PUs, cross-tabulations, kappa and prevalence- and bias-adjusted kappa (PABAK) statistics will summarise the extent of agreement of reporting of Category 2 PU status at skin sites between the independent member of the team, CRN/RHCP and photography assessments.

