### Blinding

As it is not possible to blind patients or the TVT, a validation substudy, using photography with blinded central review and expert clinical assessment of the skin sites by an independent member of the team, will be conducted to assess any bias in the reporting of Category 2 or above PUs. Two approaches are being implemented: To assess the risk of over-reporting of the ulcer, the CRN/RHCP who is not independent will photograph each Category 2 or above PU at first observation. To assess risk of under-reporting, 10% of patients are randomised for expert clinical assessment and photography of two skin sites by an independent member (if the patient has at least one PU then a photograph will be taken at a maximum of one PU skin site and one healthy skin site). A standardised photography process will be implemented to ensure a consistent approach is used across all centres when taking and transferring photographs; the central blinded review of the photographs will be undertaken by expert clinical nurse specialists.

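### The under-reporting check names no comparison by mattress, so missed ulcers that differ between arms are not addressed as stated

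*Protocol article*

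**What the plan says.** The Blinding section of the protocol article gives the reason for the substudy, "As it is not possible to blind patients or the TVT, a validation substudy", and its purpose: it "will be conducted to assess any bias in the reporting of Category 2 or above PUs". It has two parts.

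- **Over-reporting.** Each Category 2 or above ulcer is photographed when first seen. The section on the feasibility of the blinded outcome assessment then repeats the primary analysis, "replacing the primary endpoint for those patients with a Category 2 or above PU with the assessment made in the blinded central endpoint review".
- **Under-reporting.** "10% of patients are randomised for expert clinical assessment and photography of two skin sites by an independent member". Where the patient has an ulcer, "a photograph will be taken at a maximum of one PU skin site and one healthy skin site". For the analysis, the article lists cross-tabulations first and then says that "kappa and prevalence- and bias-adjusted kappa (PABAK) statistics will summarise the extent of agreement of reporting of Category 2 PU status at skin sites", the comparison being "between the independent member of the team, CRN/RHCP and photography assessments".

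Treatment group is not mentioned for the under-reporting part. The only precision figure for agreement, in the Sample size section, is for one kappa over all photographs: a half-width of ±0.044 with about 1653 photographs, 65% of them Category 2 or above, and kappa of at least 0.5.

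**The concern.** In an open-label two-arm trial, the reporting bias that can create or hide a mattress effect is one that differs between arms. If the CRN/RHCP misses the same share of Category 2 or above ulcers on both mattresses, events are lost and the contrast is somewhat diluted. If the misses fall mainly on one mattress, the hazard ratio itself moves.

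The two parts of the check differ here. The over-reporting part feeds into the between-arm comparison, but it starts from patients already recorded with an ulcer and so cannot recover one that was never recorded. The under-reporting part looks for missed ulcers, but what it names is agreement between assessors, with no link to mattress. No stated analysis therefore connects missed ulcers to treatment group. A high overall kappa could be offered as reassurance about the open-label endpoint without bearing on the bias that matters most.

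**Working it through.** **1. The plan's own figure.** Inputs from the Sample size section: n = 1653, both raters' prevalence 0.65, kappa 0.5.

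- Pe = 0.65² + 0.35² = 0.545; Po = 0.5 × (1 − 0.545) + 0.545 = 0.7725.
- Half-width = 1.96 × √[Po(1 − Po) / (n(1 − Pe)²)] = 1.96 × √[0.7725 × 0.2275 / (1653 × 0.455²)] = 0.0444.
- The Fleiss-Cohen-Everitt variance gives 0.0438.

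The stated ±0.044 reproduces. It describes a single kappa over both arms.

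**2. Size of the under-reporting sample.** 10% of 2954 is about 295 patients. Two sites each gives about 590 sites, or about 295 per arm under 1:1 allocation. Assumption, not in the article: about 20% of sampled patients have one reference-positive site. That is about 30 positive and 265 negative sites per arm.

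**3. Two scenarios with the same pooled table.** Assume no false positives.

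| Scenario | Missed, arm 1 | Missed, arm 2 | Pooled: both positive / missed / false positive / both negative |
|---|---|---|---|
| Differential | 30% (9 of 30) | 0% | 51 / 9 / 0 / 530 |
| Equal | 15% (4.5 of 30) | 15% (4.5 of 30) | 51 / 9 / 0 / 530 |

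- Po = 581/590 = 0.985.
- Pe = (60 × 51 + 530 × 539)/590² = 0.829.
- Kappa = (Po − Pe)/(1 − Pe) = 0.911, from unrounded values.
- PABAK = 2Po − 1 = 0.969.

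Both scenarios give these values, because the pooled tables are identical. That holds for any choice of prevalence and miss rates with the same total. Split by arm, the differential scenario gives kappa 0.807 against 1.000.

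**4. Direction.** Transposing the pooled table, so that the 9 discordant sites become over-calls, leaves kappa at 0.911 and PABAK at 0.969. The two coefficients carry no direction. The cross-tabulation does, because the 9 sites move to the opposite cell.

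**5. What differential misses could do to the hazard ratio.** Take no true effect and an incidence of 20.5%, the mean of the design's 18% and 23%. Suppose a fraction m of events is never recorded in one arm only. Apparent HR = ln(1 − 0.205(1 − m)) / ln(1 − 0.205).

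- m = 0.10: ln(0.8155)/ln(0.795) = 0.89.
- m = 0.20: ln(0.836)/ln(0.795) = 0.78, against the design value of 0.759.

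Here m is a patient-level loss over the whole follow-up, not a miss at one site on one day.

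**6. Precision of a by-arm comparison.** Half-width = 1.96 × √[p₁(1 − p₁)/n + p₂(1 − p₂)/n], with n reference-positive sites per arm.

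- n = 30, 5% v 20%: 1.96 × √[(0.0475 + 0.16)/30] = 0.163.
- n = 30, 5% v 25%: 1.96 × √[(0.0475 + 0.1875)/30] = 0.173; power about 59%.
- n = 15, 5% v 25%: 0.245; power about 33%.
- n = 60, 5% v 25%: 0.123; power about 88%.

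**The case against.** The strongest reply is that the article says neither pooled nor overall. It is silent on layout, and whether a validation table is also shown by arm is a detail that an analysis plan commonly settles. The Statistical analysis section promises such plans before any analysis, and the objective is labelled feasibility. This stands in part: the silence alone is not an error, and an unseen plan may already contain the split. But the article does choose the statistics for this check, justifies the photograph review by one kappa over all photographs, and says by treatment group elsewhere (adverse events, missing data). The Blinding section also states a bias purpose, not feasibility alone.

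A reader might infer three stronger things that the document does not support.

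- **That the check has no direction.** The same sentence lists cross-tabulations, whose off-diagonal cells separate under-calls from over-calls.
- **That the substudy cannot detect differential reporting.** Allocation is known for every sampled patient, so a by-arm table needs no change of design.
- **That PABAK hides missed ulcers.** It equals 2Po − 1, so each miss lowers it.

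It is also fair to object that site-level miss rates do not translate directly into a hazard ratio. Skin is assessed twice weekly to day 30 and weekly after that, so an ulcer missed once may be recorded later. That stands.

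**Conclusion.** The point holds in a limited form. As stated, the under-reporting analysis does not address misses that differ by mattress, and the over-reporting analysis cannot fill the gap. That pooled kappa and PABAK cannot distinguish differential from equal misses is an algebraic fact and rests on no assumed value. The 0.911 and 0.969 are illustrations that rest on the assumed 30 reference-positive sites per arm.

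The possible effect on the hazard ratio (about 0.89 or 0.78 with no true effect) is a bound under persistent, one-sided loss of 10% or 20% of events. It is not a forecast. Nothing in the article suggests that such loss occurs, or that high agreement would be taken as proof of an unbiased endpoint. No sample-size figure changes. This is a worthwhile, inexpensive improvement to the analysis wording, not a flaw in the design.

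**What to change.** In the section on the feasibility of the blinded outcome assessment, state that the following will be reported by mattress group:

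- the cross-tabulations of the CRN/RHCP against the independent assessor and against the photograph review;
- the proportion of reference-positive Category 2 or above sites that the CRN/RHCP recorded as below Category 2, with the between-arm difference and its 95% CI.

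Keep kappa and PABAK as secondary summaries. The over-reporting sensitivity analysis already enters the between-arm comparison and needs no change.

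The cost is a sentence or two of wording, since the data are already to be collected. The drawback is low precision, as set out in the working, and more so if the trial stops early with a smaller sample. The text should therefore also say that an interval including zero is not evidence that differential under-reporting is absent.

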#### Missing data

The pattern of missing data over time and by treatment group will be assessed. If assumed to be missing at random (MAR), multiple imputation will be considered. If the data are thought to be missing not at random (MNAR) then appropriate methods such as pattern mixture models will be explored.

### Economic evaluation

#### Within-trial economic evaluation

The expected costs and outcomes will be estimated for each treatment group up to 90 days post randomisation; based upon the observed outcomes and resource utilisation collected during the trial. The outcome measure used in the primary economic evaluation will be the quality-adjusted life year (QALY), using utilities derived from the EQ-5D-5L. A secondary analysis will use PUQoL-UI, a condition-specific utility measure derived from the PU-QoL measure [19]. The resource use data collection will focus on those incurred by the NHS including length of stay in hospital, use of hospital outpatient facilities, contact with community-based healthcare services and utilisation of supported living such as care and nursing homes. Unit costs will be obtained from national databases such as the NHS Reference costs [31] and the Personal Social Services Research Unit (PSSRU) costs of health and social care [32]. Other costs will be estimated in consultation with the finance departments of centres recruiting to the trial. Within-trial QALYs and resource cost for a subsample of trial patients will be estimated. Due to the short time horizon for the within-trial analysis, discounting will not be required. Non-parametric bootstrap will be used to estimate the expected costs and outcomes for each group and the associated incremental cost-effectiveness ratio for APM versus HSF. The results of the bootstrap will be used to construct a cost-effectiveness acceptability curve (CEAC), using a range of values of willingness to pay per incremental QALY.

